## Abstract

**Background:**

Maxillomandibular bone defects arise from maxillofacial injury or tumor/cyst removal. While the standard therapy for bone regeneration is transplantation with autologous bone or artificial bone, these therapies are still unsatisfactory. Autologous bone harvesting is invasive and occasionally absorbed at the implanted site. The artificial bone takes a long time to ossify and it often gets infected. Therefore, we have focused on regenerative therapy consisting of autologous bone marrow-derived mesenchymal cells (BM-MSCs), which decreases the burden on patients. Based on our previous research in patients with maxillomandibular bone defects or alveolar bone atrophy using a mixture of BM-MSCs, platelet-rich plasma (PRP), thrombin, and calcium, we confirmed the efficacy and acceptable safety profile of this treatment. In this investigator-initiated clinical study (the TEOM study), we intended to add β-tricalcium phosphate (β-TCP) owing to large defect with patients. The TEOM study aimed to evaluate the efficacy and safety of bone regeneration using mixtures of BM-MSCs in patients with bone defects resulting from maxillofacial injury, and tumor/cyst removal in the maxillomandibular region.

**Methods:**

The TEOM study is an open-label, single-center, randomized controlled study involving a total of 83 segments by the Fédération Dentaire Internationale numbering system in maxillomandibular bone defects that comprise over 1/3 of the maxillomandibular area with a remaining bone height of ≤10 mm. The primary endpoint is rate of procedure sites with successful bone regeneration defined as a computed tomography (CT) value of more than 400 and a bone height of more than 10 mm. Our specific hypothesis is that the number of required regions was calculated assuming that the rate of procedure sites with successful bone regeneration is similar and the non-inferiority margin is 15.0%.

**Discussion:**

The TEOM study is the first randomized controlled study of regenerative treatment using BM-MSCs for large maxillomandibular bone defects. We will evaluate the efficacy and safety in this study to provide an exploratory basis for the necessity of BM-MSCs for these patients.

**Trial registration:**

This trial was registered at the University Hospital Medical information Network Clinical Trials Registry (UMIN-CTR Unique ID: UMIN000020398; Registration Date: Jan 15, 2016; URL: https://upload.umin.ac.jp/cgi-open-bin/ctr_e/ctr_view.cgi?recptno=R000016543).

## Background

Maxillomandibular bone defects occur as a result of maxillofacial injury or surgery for maxillofacial tumors/cysts. Individuals with maxillomandibular bone defects may face limits in their daily living activities because of difficulty of eating without teeth, and unusual facial features; hence, it can have a major impact on the quality of life (QOL) of patients. While the standard therapy for these conditions is transplantation of autologous bone from the ilium, the tibia and any other bones, it is invasive for patients and hospitalization is necessary, further side effects such as infection and hematoma can arise [1]. In addition, bone grafts are occasionally absorbed at the implanted site depending on time [2, 3]. The other currently used therapy is the application of artificial bone (e.g. β-TCP, hydroxyapatite) at the defect area [4]; however, it is known that it takes a long time for ossification in cases of large defects and the implanted site often gets infected [5]. Another potential therapy is using a growth factor such as BMP-2 [6], but its efficacy has not been established in Japan and severe complications (e.g. edema in head and neck region) arise occasionally [7]. These treatments are still unsatisfactory; therefore, new regenerative therapies are required.

Meanwhile, bone regenerative cell therapy has been focused on in several experimental studies [8, 9]. We previously confirmed that transplantation of cultured BM-MSCs with PRP, thrombin, and calcium improved bone volume in non-clinical and clinical studies in patients with maxillomandibular bone defects or alveolar bone atrophy [10–19]; however, these clinical studies were a non-comparative single-arm design. Therefore, we planned a preliminary randomized controlled clinical study with the objective of confirming the efficacy of BM-MSCs in patients with maxillomandibular bone defects. In other words, we compare the efficacy and safety clinically of the mixture of “PRP, thrombin, calcium, β-TCP, and BM-MSCs” (BM-MSCs group), or the mixture of “PRP, thrombin, calcium, and β-TCP” (control group). We intend to add β-TCP as a prosthetic bone due to patients with larger defects in this clinical study than in previous clinical studies [10, 13–19].

In this article, we provide the detailed design of this investigator-initiated clinical study in adult jawbone defect patients as an exploratory study in Japan (the TEOM study). Incidentally, the main design of this trial is undergoing the process of approval by the Advanced Medical Care B program of the Ministry of Health, Labour and Welfare (MHLW), which is one of the unique systems in Japan and able to evaluate as a novel medical technology whether to be approved by the Central Medical Council on Social Insurance for coverage by public health insurance or not, based on its efficacy and safety [20].

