## Methods/design

### Overall design and objective

The primary objective of this clinical study is to evaluate the efficacy and safety of bone regeneration therapy using tissue engineering materials including BM-MSCs in patients with maxillomandibular bone defects resulting from maxillofacial injury, or tumor/cyst removal. The TEOM study is an open-label, single-center (Nagoya University Hospital, Japan), randomized controlled study involving a total of 83 regions (BM-MSCs group: control group = 55 regions: 28 regions) by the Fédération Dentaire Internationale numbering system in patients with large jawbone defects. Maximum patient number is 29 (BM-MSCs group: control group = 19 patients: 10 patients) with at least 3 defect segments per patient thereof. A flow diagram of the TEOM study is shown in Fig. 1. The primary endpoint of this study is the rate of procedure sites with successful bone regeneration that satisfies both of the following definitions; i) CT value is at least 400, and ii) Bone height is over 10 mm. We decided as a specific hypothesis that the rate of patients who fulfil the primary endpoint criteria is similar in both groups, and the non-inferiority margin is 15.0%. Additionally, we will consider whether or not secondary endpoints in the BM-MSCs group will be superior to those in the control group.

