### Preparation and application of tissue engineered materials

Autologous BM-MSCs are cultivated from the iliac crest bone marrow aspirate for about 6 to 8 weeks as per previously reported methods [10, 13–19]. Before incubation of BM-MSCs, the adequate quantity of serum is prepared by dividing the blood samples several times. Moreover, the patient’s own PRP is prepared on the day before the application of tissue engineered materials. The other components of the tissue engineered materials, thrombin (Thrombin oral/topical 5000 units “JB” or Thrombin oral fine gran. 5000 units), calcium (Calcium Chloride “Yamazen”), and β-TCP (OSferion) are purchased from Japan Blood Products Organization (Tokyo, Japan), Yamazen Corporation (Osaka, Japan), and Olympus Corporation (Tokyo, Japan), respectively.

A 10% Calcium chloride solution is prepared in advance, and thrombin (5000 units) is dissolved in 5 mL of the 10% calcium chloride solution. The mixture of BM-MSCs (about 1 × 10^7^ cells) and PRP (2.0 mL per 3.0 mL defect) is combined with the thrombin solution (0.5 mL per 3.0 mL defect). After the contents start to have a gel-like appearance, they are mixed with β-TCP (0.5 g per 3.0 mL defect). The appearance of the mixture of BM-MSCs, PRP, thrombin, calcium, and β-TCP is shown in Fig. 2. BM-MSCs are not included in this mixture for the control group. Next, the mixture is injected to the bone augmentation site following applied operation such as guided bone regeneration, or sinus floor elevation after meticulous debridement.

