As a general rule, the primary endpoint should reflect clinically relevant and meaningful effects [21]; therefore, we selected the rate of implanted sites with successful bone augmentation as the primary endpoint of the TEOM study. The definition of successful bone regeneration is the consideration as to whether the strength of augmented bone site is able to place a dental implant or not.

The secondary endpoints are as follows:Regenerated bone height by facial CT and panoramic X-ray imagePercentage of the regenerated bone height over the height of the initial defect by facial CT and panoramic X-ray imageCT valueRate of successful implant placementTime from transplantation to implant placementSurvival rate and time of dental implantTooth mobility by the implant stability meters from Osstell (SASAKI Co., Ltd. Aich, Japan)Masticatory force by Occlusal Force-Meter (GM10, Nagano Keiki. Tokyo, Japan)Histological assessmentAdverse eventLaboratory tests

In addition to achievement of the primary endpoint criteria, the clinical meaning of additional BM-MSCs in bone augmentation will be considered comprehensively according to these secondary endpoint results.

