### Sample size calculation

We assume that the rates of ‘Successful bone regeneration’ as a primary endpoint are commonly 95% in the two groups based on our clinical pilot study [14]. The non-inferiority margin is set to be 15.0% as a clinically acceptable difference.

With 83 sites per group, there was 80% power to examine the non-inferiority of the BM-MSCs group relative to the control group under the assumption of a two-sided significance level of 5.0% and an allocation ratio of 2: 1 to the BM-MSCs group or control group.

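### With a control that is the same mixture without cells, meeting the non-inferiority primary endpoint is the expected result for inert cells and cannot by itself confirm BM-MSC efficacy

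*Protocol article*

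**What the plan says.** **Aim.** Background states that the investigators "planned a preliminary randomized controlled clinical study with the objective of confirming the efficacy of BM-MSCs in patients with maxillomandibular bone defects". The abstract's Discussion says the trial is "to provide an exploratory basis for the necessity of BM-MSCs for these patients".

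**Comparison.** Background sets the mixture with BM-MSCs against the mixture without them. The section on preparing the materials confirms it: "BM-MSCs are not included in this mixture for the control group".

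**Primary hypothesis.** Overall design and objective fixes it as "the rate of patients who fulfil the primary endpoint criteria is similar in both groups, and the non-inferiority margin is 15.0" per cent. Sample size calculation takes success rates that "are commonly 95% in the two groups based on our clinical pilot study". Statistical analysis compares the lower 95% confidence limit with the margin.

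**Superiority.** Overall design and objective says "we will consider whether or not secondary endpoints in the BM-MSCs group will be superior to those in the control group". Response variables lists 11 secondary endpoints and adds that "the clinical meaning of additional BM-MSCs in bone augmentation will be considered comprehensively according to these secondary endpoint results".

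**The concern.** This is an add-on comparison: everything plus cells against everything without cells. In such a design, similar success rates are what an inactive additive would produce. A non-inferiority test can rule out a loss of 15 points, but it cannot separate cells that help from cells that do nothing. The one test with a margin, a power and a decision rule therefore answers a different question from the stated aim. The question the aim does pose, whether the cells add anything, is left to an overall judgement of secondary results with no endpoint named in advance. At stake is what the trial may conclude when its primary endpoint is met.

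**Working it through.** **Inputs.** 95% success in both arms, margin 15 points, two-sided 5% (2.5% on the side that matters), 80% power, allocation 2:1 (Sample size calculation). 83 regions in total, 55 BM-MSCs and 28 control, in at most 29 patients (Overall design and objective). The sample size section attaches 83 to each group; the abstract, the design section and the enrolment target make it the total, which I use. The decision rule is printed without a minus sign. I read it as a lower limit above −15 points, since a limit above +15 is out of reach at a 95% control rate.

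**The plan's own figure.**
- Control sites = 0.95 × 0.05 × (1 + 1/2) × (1.96 + 0.84)² / 0.15² = 24.9, so 25 + 50 = 75 sites.
- The stated 83 does not follow from these inputs by this formula. An unstated 10% dropout would give it (74.6/0.90 = 82.8). The point below does not depend on this.
- At 55:28, SE = √[0.0475 × (1/55 + 1/28)] = 0.0506, and power = Φ(0.15/0.0506 − 1.96) = Φ(1.00) = 0.84.

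**What that power means.** It is computed at a true difference of zero. In an add-on comparison, a zero difference means inert cells, so the plan's power is the probability that inert cells pass.

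**Exact check.** I enumerated all binomial outcomes at 55:28 with independent segments and counted those with a lower limit above −15 points. The plan names the Clopper-Pearson method, which is for a single proportion, so the interval for the difference is not determined; I give two.

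| True success, cells v control | Newcombe | Wald |
|---|---|---|
| 95% v 95% (inert) | 0.86 | 0.90 |
| 90% v 90% (inert) | 0.64 | 0.63 |
| 80% v 80% (inert) | 0.43 | 0.35 |
| 93% v 95% (slightly worse) | 0.69 | 0.74 |
| 90% v 95% (worse) | 0.42 | 0.45 |

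At 95% v 95%, a superiority rule (lower limit above 0) would be met in favour of the cells only about 0.6% of the time with Wald limits. That rule does separate inert from active cells.

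**Clustering.** The intraclass correlation is not in the article, so these values are assumptions. With design effect 1 + (m − 1) × ICC applied to the variance, at 95% v 95% and under an analysis that allows for clustering:
- m = 83/29 = 2.86 segments per patient: 0.84 (ICC 0), 0.72 (0.2), 0.57 (0.5).
- m = 28/4 = 7, as enrolled so far: 0.84 (ICC 0), 0.52 (0.2), 0.32 (0.5).

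**Room for superiority on the same endpoint.** A 95% control rate leaves at most 5 points to gain. Exact power at 55:28 with independent segments and Newcombe limits is 0.16 at 100% v 95% (0.05 with Wald limits). It would be 0.56 at 95% v 80% and 0.87 at 95% v 70%, but those control rates are assumptions that the article does not give.

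**The case against.** The best defence is that the authors do not rest efficacy on the non-inferiority test. They call the study preliminary and exploratory, they use the word confirming only in Background, and they say the meaning of the added cells will be judged from the secondary results as well as the primary criteria. This stands as mitigation. It shows that the authors see the primary test as insufficient, but the article still gives its only margin, power and decision rule to a question that cannot serve the aim.

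Several stronger readings are tempting and are not supported:

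- **Inert cells simply pass.** They pass with high probability at the plan's rates and independent segments. The probability falls with lower true rates or clustering, as shown above.
- **Only descriptive statistics are planned for the secondary endpoints.** Statistical analysis also provides for two-sided tests at P < 0.05 and Kaplan-Meier summaries, and refers to an analysis plan that is not shown. Model and covariates may properly sit there. What the article itself does is pose a superiority question without saying which endpoint answers it.
- **The cells have no offsetting advantage over this control.** Background says of artificial bone that "it takes a long time for ossification in cases of large defects and the implanted site often gets infected", and the secondary endpoints include time to implant placement and adverse events. Similar success with faster or safer healing would be a coherent case for non-inferiority. The article does not make that case, and its remark concerns artificial bone rather than the PRP mixture, but a flat denial goes too far.
- **Planning at equal rates is an error.** It is routine for non-inferiority. It matters here only because the comparison is add-on and the aim is efficacy.
- **The insurance review would take a met primary endpoint as proof of efficacy.** The article links the programme to coverage based on efficacy and safety, but nothing in it says how the result would be read.

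**Conclusion.** The point holds as a mismatch between aim and primary hypothesis. A positive primary result is the expected outcome for inert cells: probability about 0.84 to 0.90 at 95% in both arms, 55:28, with independent segments and the rule read as −15 points. Lower true rates or clustering reduce the figure, but they do not give the test any ability to tell active cells from inert ones. Non-inferiority alone therefore cannot confirm efficacy or show necessity, and the article fixes no superiority test that could. The logic does not depend on how 83 was derived or on which interval is used. Calling the study exploratory tempers the claim but does not resolve the mismatch.

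**What to change.** 1. Reconcile the aim with the hypothesis. State that a met primary endpoint supports only the conclusion that the cell mixture is not worse by 15 points than the same mixture without cells.
2. Once non-inferiority is met, test superiority on the same endpoint (lower limit above 0) in fixed sequence. This step costs no alpha. Say openly that power is low at a 95% control rate, about 16% even at 100% v 95%.
3. Name one continuous secondary endpoint already being collected, for example regenerated bone height on CT, as the efficacy test, analysed with allowance for segments clustered within patients. Place it next in the sequence or split alpha with step 2, and decide which in advance: behind a step with 16% power it would seldom be reached, whereas a split lowers the level for each test. The article gives no effect size or spread for such an endpoint, so its power still has to be worked out.
4. Require a superiority result from step 2 or 3 for any efficacy claim.

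The cost is a narrower claim from a positive primary result and a protocol modification that goes to committee review while an open-label trial is recruiting. No new data are needed. The article reports 28 segments in 4 patients enrolled, so the change can still be made well before recruitment ends.

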## Methods/design

### Overall design and objective

The primary objective of this clinical study is to evaluate the efficacy and safety of bone regeneration therapy using tissue engineering materials including BM-MSCs in patients with maxillomandibular bone defects resulting from maxillofacial injury, or tumor/cyst removal. The TEOM study is an open-label, single-center (Nagoya University Hospital, Japan), randomized controlled study involving a total of 83 regions (BM-MSCs group: control group = 55 regions: 28 regions) by the Fédération Dentaire Internationale numbering system in patients with large jawbone defects. Maximum patient number is 29 (BM-MSCs group: control group = 19 patients: 10 patients) with at least 3 defect segments per patient thereof. A flow diagram of the TEOM study is shown in Fig. 1. The primary endpoint of this study is the rate of procedure sites with successful bone regeneration that satisfies both of the following definitions; i) CT value is at least 400, and ii) Bone height is over 10 mm. We decided as a specific hypothesis that the rate of patients who fulfil the primary endpoint criteria is similar in both groups, and the non-inferiority margin is 15.0%. Additionally, we will consider whether or not secondary endpoints in the BM-MSCs group will be superior to those in the control group.

**Fig. 1 Fig1:**
[figure not shown]
Flow diagram of the TEOM study. This flow diagram is consisted of 2 step, ‘Before randomization’ and ‘After randomization’. In the ‘Before randomization’, patients will be randomized to BM-MSCs group or control group. The outline of procedure in each group is shown in the ‘After randomization’

### Selection of subjects

In this study, we would like to examine the effect of BM-MSCs in patients with larger bone defects than those in our previous reports [10, 13–19]. Therefore, we decided to select patients who have a maxillomandibular bone defect that comprises over 1/3 of the maxillomandibular area, because implant surgery after bone regeneration in this defect size is reimbursed under Japanese National Health Insurance.

The detailed inclusion criteria are as follows:Patients who require bone regeneration satisfying all of the inclusion criteria as follows: Patients who have a maxillomandibular bone defect that comprises over 1/3 of the maxillomandibular area with a remaining bone height of ≤10 mm due to maxillofacial injury or tumor/cyst removal. Patients who had surgical tumor removal in the maxillomandibular region must not have had a relapse/metastasis during a 5-year observation period following the procedureAged 20 years or abovePatients who have received plaque control instructions from a dentist or a dental hygienist and are in good management of itPatients that can provide signed informed consent

The main exclusion criteria are as follows:Patients with bone defects as a result of periodontitisPatients for whom surgical procedure is prohibited e.g. severe heart disease, congenital coagulation factor deficiency, leukemia, dialysis, end-stage malignant tumorPatients with or with a history of infection e.g. Hepatitis B, Hepatitis C, HIV, HTLVPatients with diabetes that is not well-controlledPatients taking bisphosphonates for more than 3 months or denosumab for more than 6 monthsPatients with or with a history of malignant tumor within the last 5 yearsPatients taking steroids or immunosuppressive drugs who cannot stop such medication for 4 weeks after trial interventionPatients in a serious condition of certain diseases (e.g. collagen disease, metabolic bone disease, immunodeficiency disease, metabolic disease, endocrine disease, blood disease, liver disease)Patients with difficulty in bone marrow aspirationPatients with difficulty in achievement of Hb ≥ 11 g/dL at preoperative examinationPatients with contraindications to local anestheticsPatients with a history of hypersensitivity to antibiotics, antifungals, thrombine products, or bovine blood-derived productsPatients taking hemocoagulase products, tranexamic acid products, or aprotinin productsFemale patients who are pregnant, suspected to be pregnant, breastfeeding, or those who do not agree to practice contraceptionAny other patients whom the trial investigator deems ineligible for this study

### Registration and informed consent

Patients are registered as candidates for this study after providing a written informed consent form. After the investigators have confirmed that they meet all eligibility criteria, the patients are enrolled via an electronic data capture system (Viedoc™, PCG Solutions Ab. Uppsala, Sweden), with subsequent randomized assignment to either the BM-MSCs group or control group by the minimization method. Allocation factors are shown as follows: i) the number of regeneration segments (< 4 segments, 5 to 6 segments, > 7 segments), ii) the method of applied operation (sinus floor elevation, any other method of operation, sinus floor elevation with any other method of operation), bone regeneration site (maxilla, mandibular, both).

